### Outcome measures

#### Primary outcomes

Trained and blinded assessors will conduct all outcome assessments.

The primary outcomes are the change in muscular strength and physical function among older people compared with different time points, i.e. at the baseline, and after 3, 6 and 12 months. The outcomes include risk of falls (Chinese version of Fall Efficacy Scale-International) and fall incidence, right-hand and left-hand grip strength, 6-meter walk test, SARC-CalF, Timed Up and Go test (TUG), Berg Balance Scale (BBS), functional reach test, skeletal muscle mass and fat mass.

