Chinese version of Fall Efficacy Scale-International: This is a validated measurement of fall efficacy with 16 questions regarding confidence of fall prevention at different situations on a four-point scale ranging from “not at all concerned” to “very concerned”. The score ranges from 16 to 64 and a lower score indicates a low fear of falling [35]. A perceived fear of falling is defined as points ≥ 20 [36].History of falls and fall incidence: A fall is defined as “an unexpected event in which the participant comes to rest on the ground, floor, or lower level, with or without injury” [37]. The history of falls including number, circumstance and severity in the previous 12 months will be assessed at the baseline [17]. The participants will be required to record their fall incidence prospectively in their diaries. The project assistant will also contact the participants regularly to ensure that they record the correct information.Right-hand and left-hand grip strength: This measurement will be performed by using a hand dynamometer (Takei Scientific Instruments Co. Ltd, Tokyo, Japan). The participants will be instructed to stand with their elbow extended and squeeze the dynamometer as hard as they can. Three attempts for both hands will be allowed and the mean of three scores will be counted [16].6-metre walk test: This is the test to assess the gait speed of the participants. The participants will be asked to walk as fast as possible without running for 10 m, which comprises a 2-metre approach, 6 m for time measurement and 2 m beyond the measurement. The units of this measurement are in seconds and will be divided by 6 to calculate the gait speed in m/s. Two attempts will be allowed and the mean of two scores will be counted [17].SARC-CalF: This is used to screen sarcopenia. It consists of six components namely strength, assistance in walking, rising from a chair, climbing stairs, falls and calf circumference [38, 39]. According to the Asian Working Group for Sarcopenia 2019 [27], diagnosis of possible sarcopenia includes SARC-CalF ≥ 11, handgrip strength (M:<28 kg, F < 18 kg) and 6-metre walk test < 1.0 m/s.Timed Up and Go Test: This is a test of functional lower-limb mobility. The participants will be seated with arms resting on the armrests. They will be asked to walk for 3 m, return to the chair, and sit down again. The time will be counted from standing to sitting back on the chair. Three attempts will be allowed and the mean of three scores will be counted [16].Berg Balance Scale score: This is a valid and reliable scale consisting of 14 static and dynamic balance activities. The score of each activity ranges from 0 to 4 and the total score ranges from 0 to 56 [40].Functional Reach Test: This test is used to assess dynamic bilateral stance balance. A metre ruler is fixed on the wall at participants’ shoulder height and the participants will be asked to stand next to but not touching the wall. The arm near the wall needs to be raised at 90° flexion and the third finger will be the initial position along the metre ruler. The participants will be asked to reach as far as possible without taking a step, bending their knees or falling over. The end position on the ruler will be marked. Three attempts will be allowed and the mean of three scores will be counted [17].Skeletal muscle mass and fat mass: The participants will be asked to dress in light clothing, hold the handgrips and stand still barefoot on a bioimpedance analyzer (Inbody 230, Biospace Co., Ltd, Seoul, Korea) after overnight fasting. The InBody 230 is a segmental impedance device which uses a tetrapolar 8-point tactile electrode method and two different frequencies (2 and 100 kHz). Fat mass, fat-free mass, percentage body fat and appendicular muscle mass (muscle mass of both arms and legs) are determined by the manufacturer’s algorithm of InBody 230. The appendicular skeletal muscle mass index (ASMI), expressed in kg/m^2^, is calculated by dividing the appendicular muscle mass by the square of height [41].

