
#### Secondary outcomes

The secondary outcomes evaluate older people’s experience of the exercise programmes. The measurements include exercise adherence, dropout rate, exercise maintenance, and Rosenberg Self-esteem Scale. Focus group interviews with open-ended questions will be conducted to evaluate the overall experience of older people with an emphasis on their psychological welfare, social well-being, and their acceptance of the telehealth approach.

Exercise adherence will be reflected by the attendance rate which is the percentage of exercise sessions attended by the participants during the 3-month intervention period.Dropout rate: This will be assessed by the number of participants who refuse to continue the training during the intervention phase or refuse to provide information during the maintenance phase. The details of the dropout will be recorded.Exercise maintenance: This will be measured by the Physical Activity Scale for the Elderly (PASE), weekly activity level and exercise diary of the participants at the baseline, and after 3, 6 and 12 months. PASE is a widely used questionnaire in epidemiological studies for assessing the physical activity level of older people. It comprises 12 items addressing the leisure, physical, household and work-related activities over the past week [34]. Physical activity level will be measured objectively by accelerometers (ActiGraph GT3X, Pensacola, FL, USA). The participants will wear one on their waist for seven consecutive days at the baseline, and 3rd, 6th and 12th months. Their total steps, activity energy expenditure, metabolic equivalent of task scores and physical activity levels will be estimated by the ActiLife software.Rosenberg Self-Esteem Scale: This is one of the widely used measures of self-esteem. The scale includes 10 items rated on a 4-point scale ranging from 1 (strongly disagree) to 4 (strongly agree), with higher scores indicating higher self-esteem.

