### Statistical analysis

Descriptive data of the two groups including age, risk of falls, body mass index, muscle mass, and activity level at the baseline will be analyzed by independent t-test to test the homogeneity of the physical characteristics between the two groups. We will use an intention-to-treat analysis based on all randomized participants following the guidelines on randomized controlled trials [43]. We will perform a sensitivity analysis for missing data. The Kolmogorov-Smirnov one-sample test will confirm the normal distribution of all the measurement variables. A two-way repeated measures ANOVA will be performed for all the outcome measures, accounting for the group (TE and CB) and the interaction term between group and time. The p-value will be set at 0.05 for all tests. All statistical analyses will be carried out using SPSS, version 26.0 (IBM Co., Armonk, NY) by an independent statistician who will not be involved in the outcome assessment. Missing data will be complemented by using the multiple imputation method.

Both groups of participants will also be invited to attend focus group interviews with an experienced qualitative researcher. The Theory Domain Framework will be adopted to examine the determinants of behaviour change [44]. Data analysis will follow a framework approach [45] and use Qualitative Data Analysis (QDA) Miner 5 of Provalis Prosuite, which is qualitative data analysis software.

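### Repeated measures ANOVA is fixed for every outcome, but attendance, dropout and fall incidence, as the protocol itself defines them, do not fit that model

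*Protocol article*

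**What the plan says.** The Statistical analysis section of the protocol article gives one rule for the quantitative outcomes: "A two-way repeated measures ANOVA will be performed for all the outcome measures". The same sentence goes on to name two model terms, the arm effect and its interaction with visit. It adds "The p-value will be set at 0.05 for all tests". On distributional assumptions it says "The Kolmogorov-Smirnov one-sample test will confirm the normal distribution of all the measurement variables", and it does not say what happens if a variable fails that test.

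The outcome sections then define three outcomes of a different kind:

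- **Falls.** Primary outcomes: "The outcomes include risk of falls (Chinese version of Fall Efficacy Scale-International) and fall incidence", with comparison over baseline, 3, 6 and 12 months. The baseline value is retrospective: "The history of falls including number, circumstance and severity in the previous 12 months will be assessed at the baseline". Follow-up is by diary: "The participants will be required to record their fall incidence prospectively in their diaries".
- **Attendance.** Secondary outcomes: adherence is the attendance rate, "the percentage of exercise sessions attended by the participants during the 3-month intervention period". The abstract and the Background name exercise adherence in the first study purpose, although it is classed as secondary here.
- **Dropout.** Secondary outcomes: the number of participants who decline further training, or decline to give information in the maintenance phase.

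**The concern.** A two-way repeated measures ANOVA needs the same roughly normal quantity measured on each person at two or more times. Attendance has one time, dropout is binary, and falls are sparse counts whose baseline differs from follow-up in both exposure length and method of ascertainment.

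For attendance and dropout, the sentence prescribes an analysis that does not exist or does not apply. Falls matter more, because they are a primary outcome of a programme meant to prevent them and the primary outcomes are framed as change across time points. Comparing a year of recalled falls with a few months of diary falls builds in an apparent reduction in both arms. Given the hypothesis that tele-exercise is as effective as traditional programmes, such a reduction could be read as success in both arms when nothing had changed.

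**Working it through.** The protocol gives no figure to reproduce here, so the check sets its outcome definitions against the model it prescribes.

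**1. Attendance.** With k groups and m time points, time has m − 1 degrees of freedom and the interaction has (k − 1)(m − 1). Here k = 2 and m = 1, so time = 1 − 1 = 0 and interaction = (2 − 1)(1 − 1) = 0. Neither term can be estimated. Only a two-group comparison remains.

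**2. Dropout.** There is one yes/no per person, necessarily 0 for all at baseline. It is not a repeated normal measurement.

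**3. Falls, expected counts.** Inputs:
- Rate: 29 falls per 100 people (Background), read as 0.29 per person-year. This is an assumption: the figure is for the general community aged 65 or above.
- Baseline window: 12 months (stated).
- Follow-up windows: 3, 3 and 6 months (inferred from the visit schedule, not stated).

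Expected count = rate × window length in years:
- Baseline: 0.29 × 1 = 0.29
- Months 0–3: 0.29 × 0.25 = 0.0725
- Months 3–6: 0.29 × 0.25 = 0.0725
- Months 6–12: 0.29 × 0.5 = 0.145

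The month-3 to baseline ratio is 0.0725 / 0.29 = 0.25, an apparent 75% drop at constant risk. Under a Poisson count, the chance of no fall in a 3-month window is exp(−0.0725) = 0.93.

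**4. Why the interaction can be distorted.** Let one arm have rate 0.29 and the other 0.58 throughout. The arm difference in counts is 0.29 at baseline but 0.58 × 0.25 − 0.29 × 0.25 = 0.0725 at month 3. The rate ratio is 2 at both times, yet the differences are unequal, so ANOVA on counts sees an interaction. If the arms have the same rate, the difference is zero in every window and this does not arise.

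**5. Simulation.** The prescribed ANOVA with Greenhouse–Geisser correction was simulated in 4000 runs, with 46 per arm (92 / 2), windows of 12, 3, 3 and 6 months, Poisson counts with gamma frailty of variance 1, and no clustering. Percentage of runs significant at 0.05:

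| Scenario | 0.29/yr | 0.6/yr | 1.0/yr |
|---|---|---|---|
| Time effect, constant rate, arms identical (counts) | 94 | 99.9 | 100 |
| Interaction, constant 2-fold arm difference (counts) | 21 | 37 | 51 |

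With identical arms the interaction is significant in 4–5% of runs, about its nominal level. With counts divided by window length, the false time effect falls to 4–5%. The Kolmogorov–Smirnov test rejected normality of the 3-month counts in every run.

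**The case against.** The strongest reply is that the wording is loose rather than literal. Focus groups sit under secondary outcomes yet have their own framework analysis, and adverse events follow the CONSORT harms guidance. The ANOVA may therefore be meant only for measures taken at all four visits, with dropout reported descriptively. A full analysis plan, not shown, may say so. This has some force for attendance and dropout. It does not rescue falls, which the Baseline assessment and Primary outcomes sections list among the outcomes followed over time.

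Four stronger readings are tempting and are not supported:

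- **That the plan yields false differences between arms in general.** The terms named are group and group-by-time, and the interaction test holds its level when the arms are identical. The distortion needs differing underlying rates. With only ten centres randomized that is plausible, but the protocol does not show it.
- **That the 75% drop is a forecast.** The protocol says fall incidence, not raw counts per interval, and the 3-, 3- and 6-month windows are inferred. Eligibility selects partly on a past-year fall, so the general-population rate need not apply. If falls are expressed per unit of time, the artefact from window length goes, but non-normality and the mix of recall with diary remain.
- **That people who stop their diary early count as having fewer falls.** Multiple imputation and a sensitivity analysis for missing data are planned, with regular contact and reminder calls. Nothing says a missing diary is zero.
- **That ANOVA is shown to be less efficient than a count model.** No such comparison was made. At 0.29 per year, 92 people would have about 0.29 × 92 ≈ 27 falls in a year, so power may be low under any model.

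**Conclusion.** The point holds as a mismatch between a stated rule and the protocol's own outcome definitions. For attendance it is certain: the model has no time factor and cannot be fitted. A reader might infer that half the primary objective is left unanalysable. That goes too far, because attendance is formally secondary and a simple two-group comparison suffices. For dropout, the outcome type is wrong for the model.

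For falls the mismatch is the most consequential, because they are a primary outcome. If interval counts are entered, a false time effect is close to certain (94–100% of runs) over rates of 0.29 to 1.0 per person-year, and the interaction is significant in 21–51% of runs when a constant 2-fold arm difference is assumed. These sizes rest on the inferred windows, the assumed rates, the Poisson–gamma model and independent participants. The 12-month recalled baseline against a prospective diary is explicit. If the diary were instead totalled once over 12 months, exposure would match, but there would no longer be four time levels.

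This point does not touch the continuous or scale measures taken at all four visits, such as Timed Up and Go, grip strength and Berg Balance.

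**What to change.** Replace the single sentence with a rule by outcome type:

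- **Continuous or scale measures taken at all four visits:** keep the longitudinal repeated measures model, and restrict it to these.
- **Falls:** compare diary falls between arms with a count model, for example negative binomial, with log of follow-up time as offset. Enter the baseline 12-month fall history as a covariate, not as a level of time. State the diary period analysed.
- **Attendance:** one between-arm comparison of the percentage at 3 months.
- **Dropout:** a between-arm comparison of proportions, for example by logistic regression.

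In each case use the same allowance for centre as for the other outcomes, because the Randomization and blinding section allocates centres rather than individuals. The Kolmogorov–Smirnov sentence should then refer only to the continuous measures.

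The cost is analysis wording. The trial already plans to collect everything needed, and the Trial Status section shows recruitment still open, so the change can be made before the data are complete.

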### Sample size calculation

In Hong Kong, there are 1,322,000 residents who are aged 65 years or above [29] and it is estimated that 118,980 of them suffer from sarcopenia (prevalence is 9% for those aged 65 or above [30, 31] and 264,400 of them have had at least one fall in the past year [1]. Calculations were performed using G*Power software and an assumed effect size of 0.367 based on a previous study by Benavent-Caballer et al. [32] on the Time Up and Go Test. Considering a 95% confidence level, a power of 80%, and 20% attrition rate (including mortality) [33], a sample size of at least 92 are required.

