### Baseline assessment

The details of the study will be explained to all participants, who will sign the consent form. Assessment will be performed before the intervention period, at the end of the 3rd, 6th and 12th months. The baseline assessments include the Chinese version of Fall Efficacy Scale-International (FES-I), fall incidence, SARC- CalF scoring, right-hand and left-hand grip strength, Timed Up and Go test, Berg Balance Scale, 6-metre walk test, Functional Reach Test, Physical Activity Scale for the Elderly (PASE) [34], Daily activity level, Rosenberg Self-esteem Scale and EQ-5D-3 L. The weight, body fat and skeletal muscle mass will be measured by a bioimpedance scale.

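### The planned repeated measures ANOVA does not adjust for baseline: its four-visit group effect is diluted and carries baseline imbalance, and its interaction gives no estimated difference

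*Protocol article*

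**What the plan says.** The protocol article (Statistical analysis) fixes one model for all outcome measures: a two-way repeated measures ANOVA "accounting for the group (TE and CB) and the interaction term between group and time". It does not list the levels of time, names no baseline covariate, and does not say whether the group term or the interaction decides the comparison.

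The levels of time follow from two other sections. Baseline assessment states: "Assessment will be performed before the intervention period, at the end of the 3rd, 6th and 12th months". Primary outcomes defines the outcomes as changes in strength and function, and gives the visits at which they are examined: "compared with different time points, i.e. at the baseline, and after 3, 6 and 12 months". The natural reading is four levels, with baseline as the first.

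For the comparison of the arms at baseline, the plan names age, risk of falls, body mass index, muscle mass and activity level. These "will be analyzed by independent t-test to test the homogeneity of the physical characteristics between the two groups".

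The same section also plans intention-to-treat analysis, multiple imputation and a sensitivity analysis for missing data. Randomization and blinding states that ten centres are randomised, with around ten participants each.

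**The concern.** A baseline value measured before treatment can sharpen the comparison and remove chance differences between arms. The plan collects it but uses it in two weaker ways. As a level of time, it enters the group main effect as a visit with a true difference of zero. In the t-tests, it is compared between arms, which adjusts nothing.

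The stake is precision and interpretability. The Background section hypothesises that tele-exercise is as effective as traditional programmes. That calls for an estimated difference with an interval at stated visits. A four-visit group average mixes treated and untreated time, and an omnibus interaction F test says only that the profiles differ somewhere. With about five centres per arm, a baseline imbalance large enough to matter is also plausible.

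**Working it through.** **Inputs from the protocol.** Four visits (Primary outcomes); N = 92 with 20% attrition, so 92 × 0.8 = 73.6, taken as 74 completers or n = 37 per arm; "an assumed effect size of 0.367 based on a previous study" (Sample size calculation); alpha 0.05, taken as two-sided; ten centres, so 92/10 = 9.2 per centre.

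**Assumptions not in the protocol.** 0.367 is a standardised mean difference d; SD 1 at every visit; equal correlation r between visits, shown from 0.3 to 0.9; no true baseline difference; no clustering in the power figures; centre intraclass correlation (ICC) 0.01 to 0.10 for the imbalance.

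**The plan's own figure.** The stated 92 could not be reproduced. Read as d, 0.367 requires 236 in total (295 after attrition). Read as Cohen's f for two groups, it requires 62 (78 after attrition). The software settings are not given. This neither supports nor weakens the present point.

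**Dilution.** For a sustained effect, the group main effect estimates (0 + d + d + d)/4 = 0.75d, so 0.367 becomes 0.275.

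**Power.** Noncentral F, with noncentrality λ:
- Group main effect: λ = (n/2)(0.75d)² / [(1+3r)/4], 1 df.
- Interaction: the squared deviations of (0, d, d, d) from 0.75d sum to 0.75d², so λ = (n/2)(0.75d²)/(1−r), 3 df.
- Baseline-adjusted contrast at one visit: λ = (n/2)d²/(1−r²), 1 df.
- Baseline-adjusted mean of the three follow-ups: λ = (n/2)d² / [(1+2r)/3 − r²], 1 df.

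At r = 0.5, with n/2 = 18.5 and d² = 0.1347, λ is 2.24, 3.74, 3.32 and 5.98 respectively.

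| Power, sustained d = 0.367 | r=0.3 | r=0.5 | r=0.7 | r=0.8 | r=0.9 |
|---|---|---|---|---|---|
| Group main effect, 4 visits | 40% | 32% | 26% | 25% | 23% |
| Group-by-time, 3 df | 24% | 33% | 53% | 72% | 96% |
| Adjusted, single visit | 37% | 44% | 59% | 74% | 95% |
| Adjusted, 3-df joint test | 48% | 51% | 65% | 80% | 97% |
| Adjusted, follow-up mean | 65% | 67% | 80% | 91% | 99% |

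The single-visit contrast gains about 13 points over the interaction at r = 0.3, 10 at 0.5, 6 at 0.7, 2 at 0.8, and none at 0.9. At equal degrees of freedom (3-df joint test), the gain is 24, 18, 12, 8 and 1 points. The rest of the follow-up mean's advantage comes from using a 1-df contrast.

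**Effect at month 3 only.** The main effect estimates 0.25d and has 7 to 9% power over this range of r. The interaction is unchanged, because (0, d, 0, 0) has the same sum of squared deviations. The adjusted follow-up mean estimates d/3 and falls to 14% at r = 0.6 (72% when sustained). Its advantage therefore needs a lasting effect.

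**Imbalance.** With 46 per arm, the SD of the baseline difference is √[2(1 + 8.2 × ICC)/46], which is 0.22 at ICC 0.01 and 0.28 at ICC 0.10. A difference of 0.3 SD or more in either direction then arises in about 17 to 29% of trials. For an imbalance of 0.3 SD:
- The main effect is shifted by 0.3 × (1+3r)/4, which is +0.14 at r = 0.3 and +0.28 at r = 0.9.
- The interaction contrasts over-correct by 0.3 × (1−r), which is −0.21 at r = 0.3 and −0.03 at r = 0.9.
- Baseline adjustment leaves zero on average under this model.

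**The case against.** The strongest defence is that the plan names the interaction as well as the group term, and the primary outcomes are defined as change. With baseline as a level of time, the interaction compares changes between arms. It is not diluted, and it removes baseline imbalance apart from regression to the mean. This stands. A reader might infer that the whole analysis leaves imbalance uncorrected; that is true of the main effect only.

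Three other inferences are not supported:
- That the ANOVA needs complete data at all four visits and so loses participants. The same section plans multiple imputation.
- That power is wasted whatever the data look like. The loss against the interaction depends on a correlation the protocol does not give, and at r = 0.9 a single-visit adjusted contrast is no better.
- That month 3 should be the sole primary contrast. Primary outcomes lists 3, 6 and 12 months without ranking them, and the Discussion covers both the intervention and the maintenance phase.

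It is also fair that the levels of time are inferred, and that a condensed article may leave detail to a fuller plan. But the article does not defer the model. It names one for all outcomes, and the point concerns that choice. Finally, the hypothesis is one of similar effectiveness, so power to detect a difference is only one yardstick; the precision gained applies equally to a confidence interval.

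**Conclusion.** The point holds in limited form. The named model has no baseline covariate. Its four-visit group term estimates three quarters of a sustained effect and carries baseline imbalance into the result. Its interaction handles baseline crudely and yields no estimated difference. Adjusting for the baseline already collected would help by an amount that depends on r. For d = 0.367, a single-visit contrast gains from about 13 points over the interaction down to none, and the follow-up mean gains more if the effect lasts.

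The absolute powers are illustrative. They ignore clustering by centre and take 0.367 as d. If it is f (d = 0.734), the main effect has 92, 84, 76 and 68% power at r = 0.3, 0.5, 0.7 and 0.9. The interaction has 78, 91, 99 and 100%, and the single-visit contrast 90, 95, 99 and 100%. The dilution and imbalance formulas do not depend on that choice. This is a worthwhile improvement in precision and bias, not a flaw that invalidates the trial.

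**What to change.** For continuous outcomes, replace the four-level ANOVA with a model of the 3-, 6- and 12-month values. Include the baseline value of the same outcome as covariate, plus group, time and group-by-time, and allow for repeated measures within participant. Report the baseline-adjusted group difference with its confidence interval at each visit. State that conclusions will not rest on a group main effect averaged over four visits. Describe baseline characteristics by arm and drop the t-tests.

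The cost is a change of analysis wording. Baseline is already measured, and Trial Status shows groups still to be recruited. Baseline adjustment does not replace allowing for clustering by centre, which is a separate issue and must be handled in its own right.
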